### Randomization

After signing an informed consent form, patients are randomized in a 1:1 ratio to either LILS or LSC centrally using a computerized random number generated at the moment of inclusion by a non-physician blinded to the women’s history and with no contact with the patients. Randomization will be stratified according to severity of prolapse (POP-Q stage 2, 3, or 4). The details of the series will be withheld from the investigators or to the participating gynecologists and all participants will receive unique study numbers. The subjects will be informed about the allocated operative procedure shortly after the randomization. Those who withdraw after randomization will be treated according to the preference of the gynecologist.

### Data collection

All patients will undergo routine gynecological examination, which is part of the standard procedure before surgery. This examination includes pelvic ultrasound to exclude uterine or ovarian disease, routine cervical screening, and vaginal inspection in a 45° semi-upright position for staging uterovaginal prolapse by POP-Q examination on maximum Valsalva effort in the lithotomy position. Urodynamic testing will also be performed in patients with urinary incontinence.

Demographics, medical, and obstetric history, previous pelvic floor and gynecological surgery were collected using standardized questionnaires. The anatomical success rate as scored by the POP-Q system and subjective satisfaction rate according to the Patient Global Impression of Improvement Scale (PGI-I) scale that integrates bladder, bowel, prolapse, sexual function domain, severity, bothersomeness, and condition-specific quality of life were recorded [11]. Other questionnaires included symptom severity, quality of life, and sexual activity in accordance with the Pelvic Floor Distress Inventory (PFDI-20), Pelvic Floor Impact Questionnaire (PFIQ-7) and the Pelvic Organ Prolapse/Urinary Incontinence Sexual Questionnaire (PISQ-12) scores at baseline and postoperation at 12 months. The PFDI-20 and PFIQ-7 questionnaires consist of three subscales each. PFDI-20 reflects the different perspectives of bulging symptoms (Pelvic Organ Prolapse Distress Inventory-6, POPDI-6), bowel problems (Colorectal-Anal Distress Inventory-8, CRADI-8), and urinary symptoms (UDI-6: Urinary Distress Inventory-6, UDI-6). PFIQ-7 describes the different impacts on a woman’s social life related to urinary tract (Urinary Impact Questionnaire-7, UIQ-7), bowel or rectal (Colorectal-Anal Impact Qestionnaire-7, CRAIQ-7), and vaginal or pelvic symptoms (Pelvic Organ Prolapse Impact Questionnaire-7, POPIQ-7). PISQ-12 describes sexual function in relation to prolapse or urinary incontinence. High PFDI-20 and PFIQ-7 indicate impaired function, and a high PISQ-12 score indicates good sexual function [12].

Intraoperatively, patients are assessed for operative time, blood loss, and complications. The impact of bleeding is also assessed by the measurement of hemoglobin levels 24 h after surgery. During hospitalization and in the first 6 weeks after surgery, the patients are asked to keep a diary, which contains the following items: postoperative pain measured by the Visual Analogue Score (VAS), pain medication intake and the Recovery Index-10 (RI-10) recovery questionnaire. The RI-10 recovery questionnaire is a validated quality-of-life questionnaire measuring subjective postoperative recovery.

Postoperatively, patients will visit the hospital at 6 weeks (routine postoperative consultation), 6 months, 12 months, and yearly thereafter. The total duration of the follow-up period is 5 years. Each check-up point includes answering a standardized written questionnaire regarding symptom severity, quality of life, and sexual activity (similar to the questionnaires at baseline) and a clinical examination (including POP-Q). The long-term complications in both groups are recorded.

### Interventions

Eligible women will be randomly allocated to receive either LILS or LSC. To eliminate the learning curve effect, the operation will always be performed by the same term of surgeons with more experience of performing both procedures. The detailed surgical procedure is presented in Additional file 2.

### Laparoscopic inguinal ligament suspension (LILS)

Laparoscopic hysterectomy with/without bilateral salpingo-oophorectomy was performed. A meticulous double-layered cuff closure was performed at the center of the vaginal cuff with a number 1 Vicry suture. The anterior vaginal wall was dissected from the bladder down to the bladder neck and the dissection was repeated for the posterior vaginal wall, which was prepared down to the levator ani plane. Afterward, the short arm of a self-styled cross-shaped mesh (Aspide Medical, La Talaudière, France) was placed into the vesico-vaginal space and recto-vaginal space and sutured to the anterior and posterior vaginal wall with four polyglycolic 1-0 sutures, respectively. Then, a portion of the inguinal ligament located 1–2 cm distance from the anterior superior iliac area was exposed. An extraperitoneal tunnel along the round ligament between the suspension points and the vaginal vault was created. The long arms of the mesh were introduced outside the peritoneum along the round ligament to the inguinal ligament suspension points and then fixed into the inguinal ligament/fascia. Finally, the peritoneal incision was closed so as to place the suspension mesh outside the peritoneum.

### Laparoscopic sacrocolpopexy (LSC)

The initial procedure of LSC was performed similarly to the procedures on the vaginal wall, and sutures were applied on the anterior or posterior vaginal wall similar to LILS. In LSC, a rectangular macroporous, monofilament polypropylene mesh was attached to the anterior vaginal wall with four polyglycolic 1–0 sutures. Another rectangular polypropylene mesh was attached to the posterior vaginal wall with four polyglycolic 1–0 sutures. Then, the peritoneum over the sacral promontory will be incised; the right ureter will be identified. The mesh will be tacked from the vaginal vault to the sacral promontory by using 5.3 × 3.7 mm staples to elevate the vaginal stump. The peritoneum will be closed in a manner covering the promontory part of the mesh and with a running suture covering the cervical part of the mesh.

During the same procedure, additional anterior and/or posterior colporrhaphy or incontinence surgery can be performed if necessary, according to the standard procedures of the hospital.

## Statistical analysis

### Sample size and power considerations

The sample size for this trial was estimated based on the hypothesis that both interventions are equivalent in anatomical success rate within a 1-year follow-up. A review [13] including 12 publications [14–24] showed an objective success rate of 78% to 100% for LSC. Thus, the sample size was calculated based on objective success rates of 90% within 1 year. If a two-sided alpha level of 5% was applied, then 89 individuals per group would be required to achieve a power of 1-β = 80% for a noninferiority margin of 15%. The rate of loss to follow-up without recurrence of prolapse is expected to sum up to 20%. Finally, a total of 214 participants (107 for each group) will be needed. Anatomical success rate at each follow-up point assessed by a POP-Q-examination in both study groups will be considered as primary outcome. Surgical anatomical success rate is defined as less than stage 1 (all vaginal sites at least 1 cm above the hymen on Valsalva), as scored by the POP-Q system. Noninferiority of LILS to LSC will be concluded if the lower limit of the 95% confidence interval in anatomical success rates lies above the noninferiority margin of -15% [25].

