**Methods:**

The trial is a randomized controlled trial. It compares LILS with LSC in women with stage 2 or higher uterine prolapse. The primary outcomes of this study are perioperative parameters, including surgical time, blood loss, intraoperative complications, and hospital stay as well as surgical anatomical results using the pelvic organ prolapse questionnaire (POP-Q) classification at 6 weeks, 6 months, 12 months, and annually till 5 years after surgery. Secondary outcomes are subjective improvement in urogenital symptoms and quality of life, postoperative complications, postoperative recovery, sexual functioning, and cost-effectiveness at each follow-up point. Validated questionnaires will be used and the data will be analyzed according to the intention-to-treat principle. Based on an objective success rate of 90%, a noninferiority margin of 15%, and a dropout of 20%, 107 patients are needed in each arm to prove the hypothesis with a 95% confidence interval.

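### The stated planning inputs (90% success, 15-point margin, two-sided 5%, 80% power) do not give 89 per group; rate, power and sample size need reconciling

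*Protocol article*

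**What the plan says.** The section on sample size and power in the protocol article gives every input the calculation needs:

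- Planning rate: "the sample size was calculated based on objective success rates of 90% within 1 year".
- Assumed true difference of zero: "both interventions are equivalent in anatomical success rate within a 1-year follow-up".
- Error rate: "If a two-sided alpha level of 5% was applied".
- Power and margin: "power of 1-β = 80" per cent, "for a noninferiority margin of 15" per cent.
- Result: "then 89 individuals per group would be required to achieve a power of" the stated 80%.

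The 89 is then raised to 107 per group (214 in total) for an expected 20% loss to follow-up. Noninferiority is to be concluded "if the lower limit of the 95% confidence interval in anatomical success rates lies above the noninferiority margin of -15" per cent. The randomization section fixes 1:1 allocation.

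The abstract repeats the basis: "Based on an objective success rate of 90%, a noninferiority margin of 15%, and a dropout of 20%, 107 patients are needed in each arm". No other planning rate or power appears in the article, and no formula or software is named for the sample size.

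**The concern.** A reader who puts the printed inputs into the usual noninferiority formula for two proportions gets a figure well below 89. So at least one of the planning rate, the power, or the implied formula is not what the text suggests.

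This calculation supports the trial's central noninferiority claim, and its inputs are repeated in the abstract. As printed, the reader cannot tell whether the design has 80% power at some lower success rate or roughly 90% power at 90%. The planning rate also determines how the margin reads. At 90% success, a 15-point loss takes the failure rate from 10% to 25%; at 85%, from 15% to 30%. Anyone who later judges the margin, the effect of dropout or an inconclusive result needs to know which rate was meant. The review range of 78% to 100% for sacrocolpopexy, cited in the same section, makes either rate credible.

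**Working it through.** **Inputs** (sample size section; allocation from the randomization section): p = 0.90 in both arms, true difference 0, margin 0.15, one-sided 2.5% (the lower limit of a two-sided 95% interval), power 80%, 1:1 allocation.

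**Attempt to reproduce 89 with the standard (unpooled, Wald) formula**

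n = (1.960 + 0.842)² × 2p(1 − p) / 0.15²

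- p = 0.90: variance term 0.18, n = 62.79, so 63 per group.
- p = 0.85: variance term 0.255, n = 88.95, so 89 per group.

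The printed 89 is not reproduced at the stated rate. It is 89/63 = 1.41 times the result, and it matches the formula at 85%.

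**Other methods at 90% success and 80% power**

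| Method | n per group |
|---|---|
| Farrington-Manning score | 73.5, so 74 |
| Standard formula with continuity correction | 75.5, so 76 |
| Two one-sided tests (equivalence), each at 2.5% | 84.1, so 85 |
| Null variance at the boundary (0.90 and 0.75), unpooled | 85.8, so 86 |
| Farrington-Manning with continuity correction | 86.3, so 87 |
| Null variance pooled at 0.825, alternative variance at 0.90 | 88.4, so 89 |

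The last line is (1.960 × √(2 × 0.825 × 0.175) + 0.842 × √0.18)² / 0.15² = 88.4. The first three rows are usual methods and none gives 89. The last three are less usual and conservative; the last one reaches 89.

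Changing the other settings within the standard formula does not help: one-sided 5% gives 50, 85% power gives 72, and 90% power gives 85.

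**Power of 89 evaluable per group**

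Power = Φ(0.15 / √(2p(1 − p)/n) − 1.960)

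- p = 0.90: Φ(0.15/√(0.18/89) − 1.960) = 91.6%.
- p = 0.85: Φ(0.15/√(0.255/89) − 1.960) = 80.0%.

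Exact binomial enumeration of the decision rule at n = 89 and 90% success gives:

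- Wald 90.9%
- Newcombe 89.2%
- Miettinen-Nurminen 89.2%
- Wald with continuity correction 87.2%
- exact unconditional score test 87.2%

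The most conservative variant tried, a continuity-corrected score test, gives 83.3%. All are above 80%.

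**Power after the expected loss**

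The 107 is 89 × 1.2 = 106.8, rounded up. A 20% loss from 107 leaves 107 × 0.80 = 85.6 evaluable per group.

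- p = 0.90: Φ(0.15/√(0.18/85.6) − 1.960) = 90.5%.
- p = 0.85: Φ(0.15/√(0.255/85.6) − 1.960) = 78.5%.

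**The case against.** The strongest reply is that 89 may be a correct result at 90% from a conservative formula that a journal article has left out. Pooling the null variance at the average of 0.90 and 0.75 gives 88.4, which rounds up to 89 with no change to rate, alpha, power or margin. This stands as a possible explanation. A reader who sees 88.95 at 85% success might conclude that 85% was the rate really used. The article does not support that: it mentions no such planning rate, and the match is not unique.

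A second reply is that 63 belongs to the plain Wald formula, and the article does not say which 95% interval will be used. This also stands in part. Against the usual alternatives of 74 to 85, the excess is smaller: 89/76 is 17% and 89/85 is 5%. But the equivalence figure of 85 answers a different question from the one-sided decision rule in the text, and no usual method arrives at 89. Nor does an unnamed formula alter the power that 89 patients have under the published confidence interval rule, which is well above 80% with each usual interval.

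A reader might also infer that the trial is too small. At the stated 90% rate the reverse is true: the discrepancy is conservative, and about 90% power remains after the planned loss.

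**Conclusion.** The point holds in this form: 90% success, 80% power and 89 per group cannot all be right under the stated decision rule by any usual method. The standard formula needs 63 per group, and other usual methods need 74 to 85. At 89 evaluable per group and 90% success, power is about 87 to 92%, depending on the interval.

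These figures assume equal true success rates in the two arms, one-sided 2.5%, and independent binary outcomes. The origin of 89 cannot be settled from the article. An 85% planning rate and an unstated conservative formula are both open.

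This should be fixed, but it does not threaten the trial. The margin, the decision rule and the analysis are unaffected, and if 90% is true the trial is larger than it needs to be. If 85% was the working assumption, the text is wrong about the rate, and power after the expected loss falls slightly below 80%.

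**What to change.** Name the sample size formula and reconcile rate, power and n in the sample size section, and the rate in the abstract. Which wording applies depends on what was done:

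- **If 90% is the planning rate:** keep it, and state that 89 evaluable per group gives about 92% power (Wald), or about 90% with the roughly 86 evaluable left after 20% loss from 107. If a more conservative formula or interval was used, name it and give the power under the interval to be used.
- **If 85% was the planning rate:** state it in both places, with 80% power at 89 evaluable per group and about 78% (78.5%) at the roughly 86 expected after loss. The 80% should not be presented as the power that remains after loss.

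Enrolment stays at 214 in either case. The cost is a few sentences and no change to the conduct of the trial.

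### The 20% loss allowance was added as 89 × 1.2 rather than 89 / 0.8, so 107 per group leaves about 86 evaluable women, slightly short of the stated 89

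*Protocol article*

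**What the plan says.** All the figures are in the protocol article, in Sample size and power considerations (under Statistical analysis), and the abstract repeats the last step.

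- Assumed success: "the sample size was calculated based on objective success rates of 90% within 1 year".
- Error rate: "If a two-sided alpha level of 5% was applied".
- Requirement before loss: "89 individuals per group would be required to achieve a power of 1-β = 80% for a noninferiority margin of 15" percent.
- Expected loss: "The rate of loss to follow-up without recurrence of prolapse is expected to sum up to 20" percent.
- Enrolment: "Finally, a total of 214 participants (107 for each group) will be needed".
- Abstract, Methods: "a dropout of 20%, 107 patients are needed in each arm".

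The formula that takes 89 to 107 is not written out.

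**The concern.** A loss rate is a share of the women enrolled. To finish with a required number, that number is divided by the share expected to remain. Multiplying it by one plus the loss rate always gives too few. Here 107 agrees with the multiplication and not with the division, so at the loss rate the plan expects, enrolment does not deliver the number the same paragraph calls required.

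At stake is whether the printed sample size statement is consistent. Noninferiority is to be concluded when the lower limit of the 95% confidence interval "lies above the noninferiority margin of -15" percent, and the width of that interval depends on how many women have a POP-Q result. The figures stand in both the abstract and the methods and are likely to be carried into the results report, where a reader who takes 20% off 107 will find fewer than 89.

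**Working it through.** **Inputs, all from Sample size and power considerations:** 89 per group before loss; 20% loss; 107 per group enrolled; 90% success, taken as the rate in both arms; margin 15 percentage points; two-sided 5%, that is 2.5% one-sided for noninferiority; 80% power.

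**Step 1. Reproduce the plan's figure.**
89 × (1 + 0.20) = 106.8, rounded up to 107. Exact match; 2 × 107 = 214.

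**Step 2. Inflate for 20% loss among those enrolled.**
89 / (1 − 0.20) = 111.25, rounded up to 112 per group, 224 in total. This is 5 per group and 10 in total above the plan, too much for rounding.

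**Step 3. What 107 delivers.**
107 × 0.80 = 85.6 per group. Shortfall: 89 − 85.6 = 3.4, so 3 to 4 women per group, or 3.4 / 89 = 3.8% of the requirement.
Largest loss at which 107 still leaves 89: 1 − 89/107 = 18/107 = 16.8%.

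**Step 4. A narrower reading of the loss.** The text speaks of loss without recurrence of prolapse. Assume that the 20% applies only to the 90% of women without recurrence. Overall loss is then 0.90 × 0.20 = 18%, and 107 × 0.82 = 87.7, still below 89.

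**Step 5. Effect on power, on the plan's own scale.** Assume that 89 gives exactly 80% power. Power with n per group is then Φ((1.960 + 0.842) × √(n/89) − 1.960). For n = 85.6: Φ(2.748 − 1.960) = Φ(0.788), about 78.5%. The loss is about 1.5 points.

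**Step 6. Effect on power, from the stated 90% rate.** With the unpooled normal formula and no true difference, the variance term is 2 × 0.90 × 0.10 = 0.18, and power is Φ(0.15 / √(0.18/n) − 1.960). For n = 85.6: Φ(3.271 − 1.960) = Φ(1.311), about 90.5%. The Farrington-Manning approach gives about 86% with 86 per group. Both exceed 80%.

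**Step 7. Why Steps 5 and 6 differ.** On the stated inputs the unpooled formula asks for 0.18 × (1.960 + 0.842)² / 0.15² = 62.8, that is 63 per group, and Farrington-Manning for 74. Neither gives 89. How 89 arose is a separate question, and Steps 1 to 4 do not depend on the answer.

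**The case against.** The best reply is that this has no practical consequence. On the stated 90% rate, about 86 women per group are more than the plan needs for 80% power by either method in Step 6. That stands, and it rules out a reading that a reader might draw from the shortfall, namely that the trial is underpowered or must recruit 10 more women. The documents do not support it.

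A reader might also infer that the true planning rate was 85%, because that rate reproduces 89 by the unpooled formula, and then report a power below 80% as the trial's real power. The documents do not support this either. They state 90%, and 85% is found only by working backwards. Another route, Farrington-Manning with a continuity correction at 90%, gives 87, close to 89. The protocol states neither, so the source of 89 is unknown.

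Three further replies soften the point without removing it:

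- The wording of the loss may describe a ceiling, or loss only among women without recurrence. A ceiling of 20% is still above 16.8%, and the narrower reading leaves 87.7. The abstract gives a plain dropout of 20%.
- Data analysis specifies intention to treat, and the handling of missing outcomes may be set out in an analysis plan not shown. But the plan itself adds the allowance to offset loss, so it treats lost women as not contributing to the 89.
- An article condenses its protocol. This is not an omission, however: 89, 20% and 107 are all printed.

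**Conclusion.** The inconsistency is real. The required 89, the expected 20% loss and the enrolled 107 cannot all hold on either reading of the loss examined here. The gap is 3 to 4 evaluable women per group, and 107 is enough only up to a loss of about 16.8%.

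It is a minor error. It costs about 1.5 points of power if 89 is taken to give exactly 80%, which is an assumption, since 89 could not be reproduced from the stated inputs by the usual formulas. If the stated 90% holds in both arms, power with about 86 per group is about 90% (unpooled). The error therefore concerns the accuracy of the sample size statement. It does not show that the trial is too small, and the decision rule is unaffected.

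**What to change.** Keep 214 participants. Correct the abstract (Methods) and Sample size and power considerations in one of two ways:

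1. State that 107 per group leaves 89 evaluable if loss is at most about 16.8%, in place of 20%. This is the simpler repair.
2. Keep 20%, and state that it leaves about 86 evaluable per group, with the power recomputed from the stated 90% rate and the method named (about 90% by the unpooled normal formula; about 86% by Farrington-Manning). The method behind 89 should then be named as well, or that figure and its 80% power will stand unexplained beside the new one.

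An 85% success assumption should not be introduced; the plan never made it.

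The cost is wording only, with no further recruitment and no change to the analysis. Under the first option, the loss the trial is said to tolerate becomes slightly less favourable; under the second, the number expected to be evaluable does.

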### Primary and secondary outcomes

The primary outcomes of this study included perioperative parameters such as surgical time, blood loss, intraoperative complications, hospital stay, and anatomical success rate using the POP-Q classification at 6 weeks, 6 months, 12 months, and annually till 5 years after surgery. The POP-Q system has been developed by the International Continence Society and is a reliable and reproducible method for assessing organ descent [10]. The lowest level of organ descent during Valsalva is measured relative to its distance from the hymen: points above the hymen are negative and those below are positive; vaginal support at the level of hymen is represented as ‘0 cm’. The anatomical success rate is defined as less than stage 1 (all vaginal sites at least 1 cm above the hymen on Valsalva), as scored by the POP-Q system. Secondary outcomes of this study include subjective outcome and improvement in general and disease-specific quality of life, short- and long-term complications, postoperative recovery, sexual functioning, and cost-effectiveness after LILS or LSC at each follow-up point.

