## Trial status

This trial is ongoing. The study began in March 2016, and the primary follow-up is expected to be completed by March 2018.

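### Anatomical success is primary at seven visits and the noninferiority rule names none of them, although only a 1-year rate is powered; four perioperative outcomes are also called primary without a criterion

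*Protocol article*

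**What the plan says.** All references are to the protocol article.

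- **Primary and secondary outcomes** (and, in similar terms, the Abstract): "The primary outcomes of this study included perioperative parameters such as surgical time, blood loss, intraoperative complications, hospital stay, and anatomical success rate", the last of these assessed "at 6 weeks, 6 months, 12 months, and annually till 5 years after surgery".
- **Sample size and power considerations**, on what is primary: "Anatomical success rate at each follow-up point assessed by a POP-Q-examination in both study groups will be considered as primary outcome".
- **The same section**, on what is powered: the hypothesis is that "both interventions are equivalent in anatomical success rate within a 1-year follow-up", and "the sample size was calculated based on objective success rates of 90% within 1 year". It states 80% power, a 15-point margin, 89 women per arm, and 107 per arm after allowing for 20% loss. On the error rate, "a two-sided alpha level of 5% was applied".
- **The same section**, decision rule: noninferiority is concluded when the lower 95% confidence limit for the difference in anatomical success lies above -15%. No visit is named.
- **Trial status**: the study began in March 2016 and "the primary follow-up is expected to be completed by March 2018".
- **Data analysis**: tests are judged at p < 0.05. No ordering of the primary outcomes is given.

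**The concern.** A noninferiority claim needs one defined comparison. Here the rule can be applied to seven intervals, and the text does not say whether one particular visit, any visit or every visit must meet the limit. These are different trials. If recurrences accumulate over time, the 6-week interval could pass while a later one fails, and the same data could then support opposite conclusions. If the visit is settled only after results are seen, the claim is no longer confirmatory.

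The perioperative outcomes raise a second, smaller problem. They cannot trigger the noninferiority claim. But each carries the label primary with no power statement and no criterion of its own, so a p-value below 0.05 on any of them could be reported as a positive primary result.

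**Working it through.** **1. Count.** Visits at which anatomical success is primary: 6 weeks, 6 months, 12 months, and 2, 3, 4 and 5 years = 7. Named perioperative outcomes: surgical time, blood loss, intraoperative complications, hospital stay = 4. Total named as primary: 7 + 4 = 11.

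**2. What is powered.** The only rate used is 90% within 1 year. That phrase does not itself fix the 12-month visit, because the 6-week and 6-month visits also fall within the year.

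**3. Dates.** March 2016 to March 2018 is two years. No woman can have a 3-, 4- or 5-year result by then, yet those visits are listed as primary.

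**4. The plan's own sample size.** Standard noninferiority formula, one-sided 2.5%, 80% power:

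n = [0.9×0.1 + 0.9×0.1] × (1.960 + 0.842)² / 0.15² = 0.18 × 7.849 / 0.0225 = 62.8, so 63 per arm.

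The stated 89 is not reproduced with 90% success. The same formula gives 89 with 85% in both arms. The step from 89 to 107 is 89 × 1.2 = 106.8. This is a separate matter; it is shown only because it explains why power per visit below exceeds the stated 80%.

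**5. Power per visit with 90% success and 20% loss.** Evaluable per arm: 107 × 0.8 = 85.6. Standard error: √(0.18/85.6) = 0.04586. Power = Φ(0.15/0.04586 − 1.960) = Φ(1.311) = 90.5%.

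**6. Rule read as any one of seven visits.** Assume a true difference of exactly -15 points at every visit, each interval testing at one-sided 2.5%. If independent: 1 − 0.975⁷ = 16.2%. With equicorrelated normal test statistics (the correlations are assumptions):

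| Correlation | False noninferiority |
|---|---|
| 0.9 | 5.7% |
| 0.7 | 8.9% |
| 0.5 | 11.5% |
| 0.3 | 13.7% |

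**7. Rule read as all seven visits.** The error rate is not inflated, but power falls. Assume no true difference, 90% success and about 86 evaluable per arm at every visit. Starting from 90.5% per visit, joint power is 82% at correlation 0.9 and 60% at 0.3. Starting from the plan's stated 80% per visit, it is 67% and 36%.

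**8. Perioperative outcomes.** Four tests at two-sided 5% with no true differences: 1 − 0.95⁴ = 18.5% chance of at least one false positive if independent, less if positively correlated.

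**9. All eleven.** Seven visits at one-sided 2.5% and four tests at 5%, independent: 1 − 0.975⁷ × 0.95⁴ = 31.8%.

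**The case against.** The strongest reply is that the intent can be recovered. The power calculation and the 90% rate both refer to 1 year, and a two-year span from start to the end of primary follow-up would fit about a year of enrolment plus 12 months of follow-up. Study design also speaks of a single primary endpoint. This is good evidence that 12 months was meant, and it makes the repair easy. It does not settle the point: the sentence making every visit primary comes after the power calculation in the same section, and the Abstract and the outcomes section agree with it. Nor is this detail left to an analysis plan, since the article itself fixes the primary outcome and its time points.

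A second reply is that the illustrations are unfavourable cases. A difference of exactly -15 points at all seven visits is unlikely if failures are few at 6 weeks, and 90% success with 20% loss need not hold at every visit to 5 years. That stands; the figures show the direction and possible size of the effect and are not forecasts.

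Some stronger readings are not supported:

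- A reader might infer that any of the eleven outcomes could carry the noninferiority claim. The rule is tied to anatomical success alone.
- A reader might take all four perioperative outcomes as superiority hypotheses. The Hypothesis section says only that the new operation may possibly do better on surgical time, blood loss and complications, and does not mention hospital stay.
- A reader might see the Discussion as contradicting the outcome list by making everything but surgical success secondary. It says only that secondary outcomes will matter once noninferiority is found.
- Eleven tests at 5% would give 43%, but the seven visit tests are one-sided at 2.5%, so 31.8% is the right figure under independence.

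**Conclusion.** The concern holds in this form: the decisive visit for the trial's noninferiority claim is not defined, and the text makes all seven visits primary while powering one. This must be fixed, because the conclusion can depend on which visit is used.

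Under the stated assumptions, an any-visit reading raises false noninferiority from 2.5% to about 5.7% to 13.7% (16.2% if independent), and an all-visits reading lowers joint power from 90.5% per visit to about 82% to 60%. The count, the missing visit in the rule and the date conflict rest on the text alone and need no assumption.

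The perioperative outcomes are a lesser part of the point. The fault is a primary label without power or criterion, with up to 18.5% chance of at least one false positive if the four tests are independent.

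**What to change.** In the Abstract, in Primary and secondary outcomes, and in Sample size and power considerations:

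- Name anatomical success at the 12-month visit as the single primary outcome.
- State that the confidence interval at that visit is the only basis for the noninferiority decision.
- Relabel anatomical success at the other six visits, and the four perioperative outcomes, as secondary.
- Make the Trial status wording on primary follow-up consistent with this.

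Testing the perioperative outcomes in a fixed order or with Holm after noninferiority is shown is one acceptable option, but is not needed to cure the defect.

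The cost is a protocol amendment and a registry update. Because the trial is ongoing and the Data and Safety Monitoring Board reviews all outcomes after every 25 women, the amendment should be dated, give its reason, and record that those making it had not seen comparative results. Visits and enrolment do not change; the perioperative outcomes lose only the primary label.
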